### Efficacy End Points and Definitions

The primary efficacy end points of the EPOCH study are progression-free survival and hepatic progression-free survival. The secondary efficacy end points are overall survival, time to symptomatic progression, objective response rate, disease control rate, quality of life assessment by FACT-C questionnaire, and adverse events. Definitions of these outcomes are as follows:

Progression-free survival is the time from the randomization date to the date of radiological progression or death from any cause, whichever occurs first. Radiological progression is determined by blinded central image review according to RECIST version 1.1.Hepatic progression-free survival is the time from randomization to the date of radiological progression in the liver or death from any cause, whichever occurs first. Radiological progression is determined by blinded central image review according to RECIST version 1.1.Overall survival is the time from the randomization date to death from any cause.Time to symptomatic progression is the time from randomization to ECOG Performance Status score greater than 2 points. Such deterioration in performance score is to be confirmed at one subsequent evaluation at least 8 weeks later.Objective response rate is the proportion of patients achieving a best tumor response of either complete response or partial response during the study, as assessed by blinded central image review according to RECIST version 1.1.Disease control rate is the proportion of patients achieving a best tumor response of either complete response, partial response, or stable disease during the study, as assessed by blinded central image review according to RECIST version 1.1.Quality-of-life assessment is based on the patient-reported FACT-C questionnaire. Deterioration in quality of life is a decline of at least seven points in the total FACT-C score or death, whichever occurs first. The time to deterioration in quality of life is calculated as the time from randomization to deterioration in quality of life.

TARE can cause tumor inflammation (edema) early after treatment; therefore, any tumor assessments performed within six weeks of randomization will not be included in the analysis of imaging-related efficacy end points to rule out the risk of false progression.

**Table 1 table1:** Schedule of events after randomization on day 0.

Interventions and assessments		Chemotherapy	First TARE^a^ workup and administration in TARE group	Study visits to progression	Additional TARE workup and administration^b^	Study visits until death or end of study
Description		Every 2 weeks	Replaces second cycle of chemotherapy	Every 8 weeks from day 0 (±1 week)	After hepatic progression, TARE replaces a cycle of chemotherapy	Every 8 weeks (±1 week)

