**Methods:**

EPOCH is an open-label, prospective, multicenter, randomized, phase 3 trial being conducted at up to 100 sites in the United States, Canada, Europe, and Asia. Eligible patients have mCRC of the liver and disease progression after first-line chemotherapy with either an oxaliplatin-based or irinotecan-based regimen and are eligible for second-line chemotherapy with the alternate regimen. Patients were randomized 1:1 to the TARE group (chemotherapy with TARE in place of the second chemotherapy infusion and subsequent resumption of chemotherapy) or the control group (chemotherapy alone). The addition of targeted agents is permitted. The primary end points are progression-free survival and hepatic progression-free survival. The study objective will be considered achieved if at least one primary end point is statistically significant. Secondary end points are overall survival, time to symptomatic progression defined as Eastern Cooperative Oncology Group Performance Status score of 2 or higher, objective response rate, disease control rate, quality-of-life assessment by the Functional Assessment of Cancer Therapy-Colorectal Cancer questionnaire, and adverse events. The study is an adaptive trial, comprising a group sequential design with 2 interim analyses with a planned maximum of 420 patients. The study is designed to detect a 2.5-month increase in median progression-free survival, from 6 months in the control group to 8.5 months in the TARE group (hazard ratio [HR] 0.71), and a 3.5-month increase in median hepatic progression-free survival time, from 6.5 months in the control group to 10 months in the TARE group (HR 0.65). On the basis of simulations, the power to detect the target difference in either progression-free survival or hepatic progression-free survival is >90%, and the power to detect the target difference in each end point alone is >80%.

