#### Analysis of Secondary Efficacy End Points

Comparison between treatment groups for all secondary end points will be conducted at the final analysis at one-sided alpha of .025.

Time-to-event end points (ie, overall survival, time to symptomatic progression, and time to deterioration in quality of life) will be compared between treatment groups using a log-rank test. Disease control rates and objective response rate will be compared between treatment groups using the continuity-adjusted Newcombe-Wilson test. The FACT-C score will be compared between treatment arms using a mixed linear model with baseline score and the relative time from baseline as covariates.

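### Time to symptomatic progression: a patient who deteriorates and dies within 8 weeks cannot count as an event

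*Protocol article*

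**What the plan says.** Efficacy End Points and Definitions gives the event as follows: "Time to symptomatic progression is the time from randomization to ECOG Performance Status score greater than 2 points". The next sentence sets the condition for counting it: "Such deterioration in performance score is to be confirmed at one subsequent evaluation at least 8 weeks later". Neither sentence mentions death, and the article has no exception for a patient who dies before the confirming evaluation.

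The same section does count death in its other disease and quality-of-life time-to-event end points. For progression-free survival: "Progression-free survival is the time from the randomization date to the date of radiological progression or death from any cause, whichever occurs first". Hepatic progression-free survival is built the same way. For quality of life: "Deterioration in quality of life is a decline of at least seven points in the total FACT-C score or death, whichever occurs first".

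Analysis of Secondary Efficacy End Points fixes the test: "time to symptomatic progression, and time to deterioration in quality of life) will be compared between treatment groups using a log-rank test". The level is also fixed: "Comparison between treatment groups for all secondary end points will be conducted at the final analysis at one-sided alpha of .025". No competing-risk method is named.

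Table 1 sets study visits up to progression at "Every 8 weeks from day 0 (±1 week", and later visits at the same spacing and tolerance. It also records ECOG status at the 2-weekly chemotherapy visits. Footnote g allows a remote ECOG assessment at chemotherapy visits and at the visits that run to death or study end.

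The abstract states another threshold: "time to symptomatic progression defined as Eastern Cooperative Oncology Group Performance Status score of 2 or higher".

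**The concern.** A confirmation rule is meant to screen out transient dips. Here it also screens out patients who do not live long enough to be assessed again, and theirs are the most severe deteriorations. If they leave the risk set as censored observations, the analysis treats their later course as being like that of the patients who remain, which it is not. The Kaplan-Meier curve then shows less symptomatic progression than occurred. If rapid death after deterioration is more common in one arm, that arm loses more events and looks better than it should on an end point tested at one-sided 0.025.

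A smaller problem is that the minimum interval equals the nominal visit interval. A next visit held on schedule but on the early side of its window cannot confirm.

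**Working it through.** The article gives no event count, effect size or power for this end point, so there is no figure to reproduce. The check has four steps.

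**1. What the definition does to an early death.** Take a first qualifying score at time T and death at T + s, with s under 8 weeks.
- Symptomatic progression: no evaluation at least 8 weeks after T can exist, so there is no event. In a log-rank test a patient without an event can only be censored.
- Quality-of-life deterioration, progression-free survival and hepatic progression-free survival: the death is an event unless one has already occurred.

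**2. Share of deteriorations lost.** Assumption, not in the article: survival after the first deterioration is exponential with median m months. Then

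share dying before week w = 1 − 2^(−t/m), with t = 7w/30.44 months.

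For w = 8, t = 56/30.44 = 1.840 months.

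| m (months) | t/m | 2^(−t/m) | Lost |
|---|---|---|---|
| 2 | 0.920 | 0.529 | 47% |
| 3 | 0.613 | 0.654 | 35% |
| 6 | 0.307 | 0.808 | 19% |

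**3. Visit window.** Visits anchored on day 0, each within ±7 days, are 56 − 14 = 42 to 56 + 14 = 70 days apart (6 to 10 weeks). Off chemotherapy, a next visit before day 56 cannot confirm. If each visit fell independently and evenly on the 15 allowed days, the share of gaps under 56 days would be (1 − 1/15)/2 = 46.7%. It is lower the more visits fall on the nominal day. For a patient caught this way, confirmation waits until about week 16 (t = 112/30.44 = 3.679 months), and the shares in step 2 become 72%, 57% and 35%. These figures do not apply on chemotherapy, where ECOG status is recorded every 2 weeks and a qualifying evaluation comes soon after week 8.

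**4. Does the comparison become biased?** A simulation used 1,000 runs of 210 patients per arm, with the same true time to deterioration in both arms (exponential, median 12 months). Administrative censoring was uniform over 12 to 48 months, and unconfirmed patients were censored at death or end of follow-up. Deaths without prior deterioration were not modelled. All these inputs are assumptions, except the total of 420 patients split 1:1.

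| Median survival after deterioration, control vs TARE (months) | Unconfirmed, control vs TARE | Apparent HR | Runs significant for TARE |
|---|---|---|---|
| 3 vs 3 | 37% vs 36% | 1.01 | 2.0% |
| 2 vs 2 | 49% vs 49% | 1.00 | 2.5% |
| 4 vs 2 | 30% vs 49% | 0.73 | 61% |
| 3 vs 1.5 | 37% vs 59% | 0.65 | 81% |

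The unconfirmed shares include patients whose confirmation would fall after the end of follow-up. With equal survival after deterioration the error rate holds at its nominal level and the cost is lost events. With unequal survival a null effect can look like a benefit.

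**The case against.** The strongest reply is that the article never says such patients are censored. It states a confirmation rule and a test, and a full protocol or analysis plan that is not shown might say how death before confirmation is handled. That is fair as to what the final analysis will do. It does not rescue the published definition: the article states the rule with its minimum interval, gives no exception, and includes death in neighbouring end points. Censoring follows from the definition and the log-rank test together.

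A reader might infer that the test is biased outright, or biased towards TARE. The documents do not support this. Between-arm bias needs early death after deterioration to differ by arm, and the article gives no data on that. The 0.65 and 0.73 hazard ratios come from assumed differences and show only what is possible.

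A reader might also infer that patients too ill to attend are lost in the same way, or that about half of all confirmations slip to week 16. Remote ECOG assessment covers part of the first. The second applies only off chemotherapy and only with full, even use of the window. Late confirmation need not move the event date, since the interval runs to the deteriorated score; it matters if the patient dies, recovers or is lost meanwhile.

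Finally, a symptom-only end point is a legitimate choice, death is captured elsewhere, and requiring persistence is sensible in an open-label trial. All of that stands. It supports keeping a confirmation step, but not treating a deterioration followed by death as unconfirmed.

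**Conclusion.** The point holds in a limited form. As published, the definition excludes any patient who deteriorates and dies within 8 weeks, and the planned test can use that patient only as censored. Deterioration is understated in both arms. The treatment comparison is distorted only if early death after deterioration differs between arms, and then in favour of the arm with more of it.

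The loss is 47%, 35% or 19% of deteriorations for assumed medians of 2, 3 or 6 months. These percentages rest wholly on the assumed exponential survival. They also depend on which ECOG threshold applies: under the stricter one patients would be more ill at first deterioration, so death before confirmation would be more likely. The visit-window mismatch is real but secondary and affects only part of follow-up. This is one secondary end point, and the primary analyses are untouched. The change is still worth making, because the rule discards the clearest cases of what the end point is meant to measure.

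**What to change.** Before the final analysis, and without reference to unblinded data:

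1. Count a deterioration as confirmed if it is still present at the next scheduled 8-weekly evaluation, held within its visit window, or if the patient dies before that evaluation.
2. Date the event at the first deterioration.
3. Where the first poor score comes from a 2-weekly chemotherapy visit, say which 8-weekly evaluation confirms it. The next one may be only 2 weeks away, which would undo the persistence requirement.
4. Add a sensitivity analysis with all-cause death as an event, matching the quality-of-life end point.
5. Reconcile the threshold in the abstract with the one in Efficacy End Points and Definitions.

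No new data are needed: Table 1 records ECOG status at every visit type, and deaths are collected for overall survival. There are two costs. A few deteriorations confirmed slightly under 8 weeks will count. The definition of a secondary end point will also have been amended after enrolment closed and the first interim analysis was reviewed, in an open-label trial, so the date and reason should be documented.

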**Interventions**						
	Hepatic angiogram,^99^^m^Tc-MAA^c^ scan,^d^ calculate liver volume and mass,^d^ calculate TheraSphere dose,^d^ order and administer TheraSphere	—^e^	✓	—	✓	—
	Administer second-line chemotherapy	✓	—	—	—	—
**Assessments**						
	ECOG^f^ Performance Status	✓^g^	✓	✓	✓	✓^g^
	Hematology^h^, chemistry panel, liver function tests	✓	—	✓	✓	—
	Coagulation tests^i^	✓^j^	—	—	✓	—
	Serum pregnancy^k^	—	✓	—	✓	—
	Tumor markers for colorectal cancer (serum carcinoembryonic antigen)	—	—	✓	—	—
	Record and administer any chemotherapy following second-line chemotherapy^l^	—	—	—	—	✓
	Quality-of-life questionnaire	—	—	✓	—	✓^g^
	Spiral CT^m^ or MRI^n^ of the abdomen, pelvis, or chest^o^	—	—	✓	✓	—
	Assess and report adverse events	✓	✓	✓	✓	✓
	Review and record concurrent medication	✓	✓	✓	✓	✓
	Final end point, efficacy and safety documentation, and exit patient	—	—	—	—	✓

^a^TARE: transarterial radioembolization.

^b^In lesions amenable to further TARE.

^c^^99m^Tc-MAA: technetium-99m macroaggregated albumin.

^d^Before TARE administration.

^e^Assessment or intervention was not conducted at that time.

^f^ECOG: Eastern Cooperative Oncology Group.

^g^Can be done remotely if patient is not coming in for clinic visit.

^h^Hematology tests: white blood cells with differential, hemoglobin, hematocrit, and platelets.

^i^Coagulation tests: prothrombin time, partial thromboplastin time, and international normalized ratio.

^j^Only required at chemotherapy visits as clinically indicated, that is, if patient is being followed for coagulopathy.

^k^Required for female patients of childbearing potential.

^l^All randomized patients must receive chemotherapy within 21 days of randomization.

^m^CT: computed tomography.

^n^MRI: magnetic resonance imaging.

^o^All attempts should be made to obtain imaging every 8 weeks until hepatic progression, plus confirmatory scan.

The following additional efficacy variables will be assessed:

Progression-free survival and hepatic progression-free survival by investigator assessment, with progression determined by the investigator according to RECIST version 1.1.Objective response rate, determined by the investigator, defined as the proportion of randomized patients achieving a best overall response of complete response or partial response, as defined by RECIST version 1.1.Duration of objective response will be determined for patients who had a best response of complete response or partial response. Duration of objective response is defined as the time from the first date of complete response or partial response to date of progression or death from any cause, whichever occurs first. Duration of response will be assessed separately for response determined by blinded central image review and by investigator assessment.Disease control rate, as determined by the investigator, defined as the proportion of randomized patients achieving a best overall response of complete response, partial response, or stable disease as defined by RECIST version 1.1.Duration of disease control will be determined for patients who had a best response of complete response, partial response, or stable disease. Duration of disease control is defined as the time from the first date of complete response, partial response, or stable disease until the date of progression or death from any cause, whichever occurred first. Duration of disease control will be assessed separately for response determined by blinded central image review and by investigator assessment.Depth of response, defined as the percentage change from baseline to the nadir in the sum of the longest diameters of target lesions.Posttreatment tumor shrinkage, defined as the proportion of patients achieving a decrease of at least 20% in the sum of the longest diameters of target lesions.Change from baseline in tumor marker for colorectal cancer (carcinoembryonic antigen).

### Planned Statistical Analysis

#### Sample Size Estimate

The study is a phase 3 adaptive trial, comprising a group sequential design with 2 interim analyses. The study could be stopped early for efficacy at an interim analysis based on superiority in progression-free survival but not hepatic progression-free survival.

The study is designed to detect a 2.5-month increase in median progression-free survival, from 6 months in the control group to 8.5 months in the TARE group (hazard ratio [HR] 0.71), and a 3.5-month increase in median hepatic progression-free survival time, from 6.5 months in the control group to 10 months in the TARE group (HR 0.65). On the basis of simulations, the power to detect the target difference in either progression-free survival or hepatic progression-free survival is >90%, and the power to detect the target difference in each end point alone is >80%, using log-rank tests.

The analysis of progression-free survival will be based on a group sequential design with 2 interim analyses at 50% and 70% of the required total number of 344 progression-free survival events with a stopping boundary defined by the rho family error spending function with ρ=1.5 [24]. It is estimated that a maximum of 420 patients will need to be recruited over 36 months, with a 1-year additional follow-up period, allowing for 10% of patients lost to follow-up and for whom a date of progression or death is not recorded. Although the forecasted accrual period has been increased to 60 months, this does not increase the number of patients required or affect the statistical power of the study because both the power and the timing of the interim and final analyses are based on the number of progression-free survival events rather than the number of patients. The Hochberg procedure will be used to control type 1 error for the 2 primary end points at the final analysis [25].

A simulation study, assuming that progression-free survival and hepatic progression-free survival have a correlation between 0.3 and 0.8, showed that the power to detect the target difference in either median progression-free survival (ie, HR 0.71) or median hepatic progression-free survival (ie, HR 0.65) is >90%, and the power to detect the target difference in progression-free survival or hepatic progression-free survival alone is >80%. The simulation study also demonstrated control of type 1 error at the nominal one-sided level of 0.025.

#### Populations

The intent-to-treat population will comprise all randomized patients. The per-protocol population will be analyzed according to the treatment actually received, excluding patients with major protocol deviations that may affect the efficacy evaluation. The safety analysis population will comprise all randomized patients who received study treatments at least once.

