### Randomization and Stratification

Eligible patients are randomized on day 0 in a 1:1 ratio to either the control group or the TARE group. If the study is not stopped early for efficacy, approximately 210 patients will be randomized to each group. To randomize eligible patients, the study site contacts the central randomization office where randomization will be determined using assignment by a computer-generated randomization scheme. Upon randomization, each patient is assigned an identity code. To ensure that treatment groups are balanced, patients are stratified at randomization based on the extent of liver involvement (unilobar vs bilobar disease), type of first-line chemotherapy (oxaliplatin-based vs irinotecan-based), and KRAS status (wild type vs mutant). Additional factors permitting covariate analysis are captured at randomization but are not stratification criteria. These factors have been defined based on the planned covariate analyses. Patients randomized to either the control or the TARE group who are unable to receive their planned study treatment continue to be followed under their assigned study group for the purpose of the intent-to-treat analysis.

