### Transarterial Radioembolization

In the TARE group, TheraSphere microspheres are administered in place of the second cycle of chemotherapy. The treatment approach for TheraSphere can be lobar or selective. Patients with unilobar disease receive TARE to the diseased lobe. Patients with bilobar disease receive treatment to both lobes via successive lobar infusions during the same treatment session. Biological agents must be discontinued for at least 28 days before TARE. Chemotherapy resumes 2 weeks after TARE, at which time treatment with biologic agents may be started.

Eligibility for TARE with TheraSphere microspheres is determined by evaluations that include a pretreatment angiography with technetium-99m macroaggregated albumin (^99m^Tc-MAA), followed by a^99m^Tc-MAA single-photon emission computed tomography (SPECT) or SPECT-CT scan to assess the potential for shunting microspheres to the lungs as well as the potential for the deposition of microspheres to the gastrointestinal tract. Repeat^99m^Tc-MAA may be needed for subsequent treatments to estimate cumulative lung shunt or to reassess gastrointestinal shunting. Patients are ineligible for TARE if radiation exposure to the lungs exceeds 30 Gy (or 50 Gy cumulative across all planned infusions, estimated during the dose calculation) or embolization cannot be performed to effectively block gastrointestinal blood flow from the hepatic arterial system. Randomized patients deemed ineligible for TARE continue with the planned second-line chemotherapy.

Radioembolization can be performed via a segmental or lobar approach, depending on operator preference and angiographic anatomy. The targeted administered dose is 120±10% Gy to the target volume, based on a single-compartment Medical Internal Radiation Dose model [23].

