#### Primary Efficacy End Points

##### Analysis of Primary End Points

Progression-free survival and hepatic progression-free survival will be compared between the control and TARE groups using log-rank tests. The HR and 2-sided 95% CI will be computed. Kaplan-Meier curves will also be produced.

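### Per-protocol efficacy is grouped by treatment received, although TARE suitability is tested only after randomization and only in the TARE group, so that comparison can be biased

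*Protocol article*

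**What the plan says.** The Populations section defines the set in one sentence, which begins: "The per-protocol population will be analyzed according to the treatment actually received". The rest of that sentence leaves out anyone whose major deviations could influence the assessment of efficacy. It does not list those deviations or say whether never receiving TARE is one.

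The section on Transarterial Radioembolization describes how suitability is settled: "Eligibility for TARE with TheraSphere microspheres is determined by evaluations that include a pretreatment angiography", followed by a 99mTc-MAA scan. Patients are ineligible if lung exposure is too high or if gastrointestinal flow cannot be blocked. Then: "Randomized patients deemed ineligible for TARE continue with the planned second-line chemotherapy". The schedule of events after randomization (Table 1) places this work-up in the column for the first TARE in the TARE group. The section on Screening and Eligibility has no counterpart for controls.

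The main comparison is described differently. "The intent-to-treat population will comprise all randomized patients", and under Randomization and Stratification, patients of either group who cannot be treated as planned "continue to be followed under their assigned study group for the purpose of the intent-to-treat analysis".

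**The concern.** A per-protocol set grouped by treatment received keeps the protection of randomization only if the step that decides the treatment works alike in both groups. Here it works in one. TARE-group patients are examined, and those who fail receive chemotherapy without TARE. Equally unsuitable controls are never identified and stay where they are. The regrouped control set holds its own unsuitable patients plus those of the TARE group, and the regrouped TARE set holds none. To be counted as TARE, a patient must also survive and stay fit until the procedure, a condition that controls do not face.

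The moved patients may not even match the controls in treatment. TARE-group patients may start biological agents only after TARE, whereas controls may start them with the first cycle (Figure 1 legend and Chemotherapy).

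At stake is how far a per-protocol result can be trusted in an open-label trial. If it agrees with a positive intent-to-treat result, the agreement says little. If it is positive beside a null one, it could mislead.

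**Working it through.** **Inputs from the protocol article.** About 210 patients per group, 1:1; final analysis at 344 progression-free survival (PFS) events; control median PFS 6 months; target HR 0.71; one-sided 0.025; chemotherapy starts within 21 days and is generally given every 2 weeks; TARE replaces cycle 2; scans within six weeks of randomization are not used.

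**Assumptions.** The article gives neither the share of patients unsuitable for TARE (f) nor their PFS hazard relative to other patients (g). Both are varied.

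**The plan's own figure.** It states no figure for the per-protocol analysis. Its design figure reproduces: |ln 0.71| × √(344/4) − 1.96 = 0.3425 × 9.274 − 1.96 = 1.216, which is 88.8% power in a fixed design, in line with the stated >80%. The event count is therefore a sound basis for the check.

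**Step 1: composition at f = 10%.** 10% of 210 is 21 patients per group. By treatment received, control holds 210 + 21 = 231 patients, of whom 42 (18.2%) are unsuitable. TARE holds 189, of whom none are. With no true effect, the HR at the start is 1 / [1 + 0.182 × (g − 1)]:

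- g = 1.5: 1/1.091 = 0.92
- g = 2.0: 1/1.182 = 0.85
- g = 1.0: 1.00
- g = 0.67: 1/0.940 = 1.06

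As follow-up goes on, high-hazard patients leave the risk set early and low-hazard patients accumulate. The average HR is therefore nearer 1 than the starting value when g > 1, and further from 1 when g < 1.

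**Step 2: average over the trial.** Simulation with exponential PFS, no true effect, 210 per group, analysis at event 344, no loss to follow-up, 1,000 trials per setting. Monte Carlo error of a mean log HR is about (2/√344)/√1000 = 0.003. One-sided rejection rates at 0.025 are in parentheses.

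| f | g | By assigned group | By treatment received | Unsuitable TARE-group patients excluded |
|---|---|---|---|---|
| 5% | 1.5 | 0.999 (2.4%) | 0.965 (5.9%) | 0.981 (4.6%) |
| 5% | 2.0 | 0.997 (2.0%) | 0.943 (6.0%) | 0.968 (3.2%) |
| 10% | 0.67 | 1.003 (1.7%) | 1.079 (0.6%) | 1.044 (0.9%) |
| 10% | 1.0 | 1.006 (2.5%) | 1.006 (2.4%) | 1.006 (2.6%) |
| 10% | 1.5 | 1.003 (2.5%) | 0.935 (9.2%) | 0.965 (4.9%) |
| 10% | 2.0 | 0.999 (2.1%) | 0.895 (18.7%) | 0.940 (8.1%) |
| 20% | 2.0 | 1.000 (2.9%) | 0.814 (44.5%) | 0.884 (18.0%) |

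Repeat runs at f = 10% gave HRs of about 0.93 (g = 1.5) and 0.90 (g = 2.0). The rejection rate at g = 2.0 lay between 16% and 19%.

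**Step 3: deaths before TARE.** TARE falls about 0 + 14 = 14 to 21 + 14 = 35 days after randomization. Scans before six weeks (42 days) are not used, so only deaths can be PFS events in that window. Relabeling one early death lowers the TARE group's observed-minus-expected count by about 1. The log-rank variance is about 344/4 = 86, so the log HR shifts by about −1/86 = −0.0116 per death. Two moved deaths give exp(−0.023) = 0.98, and four give exp(−0.047) = 0.95. The number of such deaths is not in the article.

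**The case against.** Five points can be made for the plan.

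- **Transfer to control is inferred.** The same sentence excludes major deviations that may affect efficacy, and the deviation list may stand in a document not shown. This stands in part. But the protocol itself prescribes continued chemotherapy for these patients, so calling them deviators is not the natural reading. Excluding them also leaves bias: at f = 10% and g = 2.0 the HR is 0.94 instead of 0.90.
- **The direction is not established.** A reader might infer that the analysis is biased in favor of TARE. The documents do not support that as a general statement. Nothing in them links lung shunting or gastrointestinal flow to PFS; equal prognosis gives no bias, and better prognosis gives bias against TARE. Only reclassified deaths before TARE always favor it.
- **Early failures are few.** Counting every PFS event in the first 0.5 to 1.0 month as moved would give an HR of 0.88 to 0.77. That does not apply here, because early scans are not used and patients must have performance status 0 to 1 up to their first study treatment.
- **Controls might move the other way.** Under Treatment for Disease Progression, controls with hepatic progression may receive TheraSphere. Read literally, the rule would move them to TARE after they have progressed, which works against TARE for PFS. This stands, and it is a further reason to reword.
- **No primary result depends on this set.** This stands. No section assigns the per-protocol population to a confirmatory test. The sentence under Analysis of Primary End Points, "Progression-free survival and hepatic progression-free survival will be compared between the control and TARE groups using log-rank tests", names no population, but patients who cannot receive their treatment are kept in their assigned group for intent-to-treat.

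**Conclusion.** The concern holds in a limited form. A suitability test applied after randomization in one group, combined with grouping by treatment received, gives a per-protocol comparison that randomization does not protect. That conclusion needs no assumption about prognosis; the size and sign do. At an assumed 10% unsuitable and no true effect, the HR is about 0.93 to 0.90 for g of 1.5 to 2.0, 1.00 for g = 1, and 1.08 for g = 0.67. Over f of 5% to 20% and g of 0.67 to 2.0, it runs from about 0.81 to 1.15. Moved deaths add roughly 1% each in favor of TARE and are probably few.

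A reader might go further and infer that the trial's main conclusion or its type 1 error is at risk. It is not: by assigned group the HR stays at about 1.00 and rejection at 2% to 3% in every setting. The weakness is confined to a non-primary analysis, but it comes from a rule the article states, not from detail left to another document.

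**What to change.** Reword the per-protocol definition under Populations:

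- Analyze the set by randomized group, and exclude only deviations that can be judged alike in both groups.
- State that not receiving TARE, where the protocol prescribes continuing chemotherapy, is not such a deviation.
- Apply grouping by treatment received to the safety population, for which the section now states no grouping.
- If an efficacy analysis by treatment received is still wanted, label it exploratory, start it from a common landmark after the planned TARE date, and do not count TheraSphere given to controls after progression as TARE.

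The cost is a change of wording; no new data are needed. The per-protocol set moves closer to intent-to-treat and so adds less as a separate view, and its estimate may be slightly less favorable to TARE.
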